#### Image analysis

MRI data will be analysed using advanced image processing techniques as below.Structural AnalysisT2 relaxation maps will be obtained from three T2-weighted images by first aligning all T2- weighted images to the T2-weighted image with the shortest echo time (TE = 27 ms) using rigid-body registration, followed by voxel-wise estimation of T2 employing a nonlinear least-squares fit. The T2w MR will be segmented using the MILXView neuroimaging platform with the UNC neonate atlas and ALBERT atlas used to provide initial priors and anatomical labelling [129–131]. Statistical analysis will use Regions-of-Interest and voxel based analysis techniques. Summary measures of T2 will be calculated within pathways delineated using tractography.Diffusion AnalysisAn extensive pre-processing and quality control procedure will be used to detect and correct image artefacts caused by involuntary head movement, cardiac pulsation, and image distortions [30]. Fractional anisotropy (FA) and mean diffusivity (MD) will be estimated from corrected diffusion data using a diffusion tensor model. Constrained spherical deconvolution implemented in MRtrix will be employed to estimate fibre orientation distribution (FOD) [132]. Whole-brain voxel based analysis of FA and MD will be performed using tract-based spatial statistics optimised for neonates [133]. Whole-brain voxel-based analysis of fibre orientation distributions will be conducted using Apparent Fibre Density (AFD) [31]. Probabilistic tractography will be performed using MRtrix. White matter pathways will be delineated using the multi-regions-of-interest approach. A number of pathways, including cortico-spinal tract, corpus callosum, superior longitudinal fasciculus and thalamic radiations, will be extracted. Summary measures of FA, MD, AFD and T2 within pathways will be calculated.Arterial Spin Labelling analysisAn extensive pre-processing and quality control procedure will be used to detect and correct image artefacts caused by motion, random thermal and physiological noise, EPI distortion, spatial-temporal denoising, correction for temporal decay and partial voluming of the signal. The CBF maps will then be calculated in absolute units $$ \left(\frac{ml}{100g\kern0.5em 60s}\right) $$, with the first equilibrium magnetization of arterial blood estimated using the calibration image (first acquired image), and GM and WM maps rescaled. Statistical analysis will use Regions-of-Interest and voxel based analysis techniques.

### EEG

Dense array EEG (dEEG) will be collected using either; i) a NicOne EEG amplifier (Cardinal Healthcare, USA) with a sampling rate of 256 Hz from 32 channels using an appropriately sized EEG cap (Waveguard, ANT-Neuro, Germany) with electrode positioning according to the international 10–20 standard, or ii) a 64-electrode high-density sensor net (HydroCel Geodesic Sensor Net, Electrical Geodesics Inc.). Each electrode is enclosed in a saline sponge, in a geodesic tension structure comprised of elastic threads EEG signals are transmitted from the sensor net electrodes to an amplifier (Electrical Geodesics Inc.) digitised and recorded via NetStation software (Electrical Geodesics Inc.).

For the EEG data i) directional relationships between channels, ii) frequency-specific amplitude fluctuations, and iii) time-varying behaviour through directional connectivity analysis and phase synchrony among channels will be examined. Electroencephalography power will be estimated in the frequency bands delta/theta (2–7 Hz), alpha (8–13 Hz), beta (14–32 Hz) to examine changes in the power and frequency of oscillations over the sensorimotor cortex as an index of corticospinal linkage and maturation [59].

The electric resting state network (eRSN) analysis will follow a multi-step procedure comprising i) pre-processing of EEG signals, ii) extracting band amplitude fluctuation envelopes at the frequency band of interest, and iii) evaluating their network characteristics within two modes of activity. Relationships between eRSN characteristics and outcome will be sought using approaches including pair-wise relationships such as mutual information measures, with testing using surrogate signals as well as different statistical testings at individual and group levels.

### Clinical measures

#### General Movements Assessment (GMs)

The GMs is a predictive and discriminative tool that involves observation of an infant’s spontaneous motor activity [66]. It can be used from preterm birth until 20 weeks CA and is carried out by videoing the infant in supine, in a calm alert state with no external stimulation. Scoring is completed from the recording with 3 full movement sequences required for pattern recognition (approximately 5 min) [66]. In the early preterm stage this may require up to an hour of video in order to select sequences of active movement, but at TEA and 12 weeks CA it may only take a few minutes. Movements are classified as normal or abnormal (poor repertoire, cramped synchronised or chaotic) in the writhing period from preterm up to 6 weeks post term. During the fidgety period from 9–20 weeks post term, fidgety movements are classified as present, abnormal or absent [66]. Infants in this study will have an assessment of their GMs in the preterm period (30–32 weeks PMA), one assessment at TEA, and one at 10–12 weeks CA. The GMs have been found to have the greatest predictive accuracy of motor outcome in two systematic reviews on the clinimetric properties of neuromotor and neurobehavioural assessment tools for use in preterm infants in the preterm period and first year of life [64, 65]. A systematic review examining the accuracy of tests to predict cerebral palsy included a meta-analysis of GMs. The pooled sensitivity and specificity were 98 % (95 % CI 73–100 %) and 91 % (95 % CI 83–95 %) respectively [10]. General Movements in the fidgety period display greater sensitivity and specificity than those in the writhing period [6, 7, 134] and have also shown an ability to predict functional severity of CP as classified by GMFCS [67]. Additionally, GMs predict cognition [68, 135, 136], minor neurological dysfunction and developmental coordination disorder [69, 137], as well as behavioral and psychiatric outcomes [70, 138].

#### The NICU Network Neurobehavioural Scale (NNNS)

The NNNS is a discriminative neurobehavioural assessment initially designed for use in prenatally substance exposed infants as part of the Maternal Lifestyle Study (MLS) [139]. It’s application for use in other high-risk infant populations including very preterm infants is now well established [64, 75, 125]. Neurobehavioural functioning is determined through evaluation of neurological and motor performance, orientation to auditory and visual stimuli, state regulation, self-soothing competence and stress signs. Forty-five items are administrated in a structured format comprising state-dependent ‘packages’, with a further 21 summary items scored. The stress/abstinence scale encompasses an additional 51 observed items. Summary scores are calculated to enable statistical analysis, and they include orientation, habituation, hypertonicity, hypotonicity, excitability, arousal, lethargy, nonoptimal reflexes, asymmetric reflexes, stress, self-regulation quality of movement and handling [140]. Training and certification is required to administer and score the assessment.

Normative data on the NNNS are available in 2 studies, with samples of 125 and 344 healthy term infants respectively, assessed within 48 h of birth [141, 142]. Data of preterm infants assessed using the NNNS at 1 month CA are available though it is important to note that the cohort is selected from the MLS sample and therefore includes infants with high social risk and drug-exposure [143]. Preterm infants display poorer neurobehaviour at TEA when compared to term controls on the NNNS [144, 73]. Significant disturbances were found in motor behaviour, tone, poorer self-regulation capacities, higher excitability scores [144], poorer orientation, lower tolerance of handling and more stress in preterm infants compared with term born infants [73]. These alterations in neurobehaviour correlated with cerebral abnormalities in white and grey matter on qualitative structural MRI [72]. Predictive validity of the NNNS has been established with neurobehaviour at term predicting motor and cognitive outcomes at 18 months, motor outcomes at 24 months and cognitive outcomes at 4.5 years [75, 145, 146]. Test-retest reliability has been established with preterm infants with correlations ranging from .30 to .44 across three time points tested (34, 40 and 44 weeks PMA) [147].

#### Hammersmith Neonatal Neurological Examination (HNNE)

The HNNE was developed for the assessment of term and preterm infants at risk of developmental delay [148–150]. It is a discriminative and predictive test that assesses posture and tone, reflexes, movements and neurobehavioural responses. It is criterion and norm referenced, with normative data from a sample of 224 healthy low-risk term infants assessed between 6 and 48 h after birth [149]. Raw scores are converted into a continuous score derived through optimality scoring with final scores ranging between 0–34, and scores <30.5 considered to be suboptimal [150]. Preterm infants have been found to have poorer scores on the HNNE compared with term born infants when assessed at TEA. In a sample of 157 infants born at <33 weeks GA mean optimality scores were 26.4 [151]. Discriminative validity was demonstrated in a normative study of a sample of 380 preterm infants (GA at birth 25–35 weeks) with a normal outcome and a sample of 85 infants who developed CP examined at TEA. Preterm infants with later outcome of CP had a greater number of suboptimal items scored compared to those preterm infants who had a normal outcome [152]. Concurrent validity has been demonstrated in 2 studies (*n* = 168 and *n* = 66), where poorer scores on the HNNE related to increasing severity of cerebral abnormality on structural MRI [72, 80]. A systematic review examining the predictive validity of the HNNE to predict an outcome of CP report a sensitivity range of 57–86 % and specificity range of 45–83 % when performed before term age (<37 weeks PMA) [78, 79]. This increases to a sensitivity range of 68–96 % and specificity range of 52–97 % when assessed in the post term period [78, 81]. Percentage agreement has been shown to be good between raters after training (>96 %) [153], however few reliability statistics are available. The infants in the present study will have the HNNE assessment at 30 weeks gestation, and TEA.

#### Premie-neuro

The Premie-Neuro is a neurological and neurobehavioural assessment tool developed by Ellison and Daily [154]. It consists of 3 subscales of 8 items each: neurologic, movement and responsiveness. Although limited published data are available for this relatively new tool, it was selected for this study for the following reasons: i) scoring of neurologic and movement subscales can be completed in even the sickest and most fragile of infants as they require minimal handling, ii) significant overlap with the HNNE and NNNS means the assessment can be scored with the addition of only 2 items overall, iii) scores are based on expected findings at differing gestational age [154]. Validity has been established for discriminating between preterm infants at high and low risk for neurodevelopmental delay, although interrater reliability was low and test–retest reliability was fair to moderate [155]. It will be scored from the combined assessment performed at 30 weeks PMA for infants in this study.

#### Neonatal visual assessment

The neonatal assessment of visual functions provides useful information on various aspects of early neonatal visual function, including ocular motility, fixation, following, acuity and attention at distance. The battery is easy to perform, does not require long training, and can be performed reliably from 32 weeks PMA [156]. It has been demonstrated to contribute to prediction of neurodevelopmental outcome in preterm babies [157–159]. The overall sensitivity and specificity of Neonatal Visual Assessment to predict 12 month CA visual scores were 90 % and 63 % respectively in 121 preterm infants [158]. In this study, infants will be assessed at TEA and 12 weeks CA.

#### Test of Infant Motor Performance (TIMP)

The TIMP is a discriminative and evaluative test of functional motor behaviour used to assess infants between the ages of 34 weeks PMA and 4 months CA [160, 161]. The test assesses the postural and selective control of movement needed for functional motor performance in early infancy and is norm referenced. Observational and elicited items are administered in a standardised procedure and the test takes 20–40 min to administer. At 12 weeks CA, the TIMP has been shown to predict 12 month motor performance with sensitivity 92 % and specificity 76 % [162] and preschool motor performance (mean age 4.75 years) with sensitivity 72 % and specificity 91 % [163]. In this study, the TIMP will be performed at TEA, and at 12 weeks CA by an assessor trained by the test author.

### Neurodevelopmental and motor outcome at 12 months

#### Medical assessment

A paediatrician experienced in infant development and diagnosis of CP will independently assess infants in this study at 12 months CA. The purpose of this assessment is to discriminate which infants are developing typically from those who are not, and to confirm diagnoses of CP or not CP [164]. It is acknowledged that 12 months CA is early to confirm a diagnosis of CP, especially in less severe cases. For this reason a structured neurological examination of posture, reflexes, muscle tone and movement will be conducted with participants classified as ‘normal’ (entirely normal neurological examination), ‘unspecified signs’ (e.g. hypotonia, asymmetric reflexes) or ‘abnormal’ (definite neurological abnormality, likely CP). In cases where CP can be confirmed, motor type and distribution will be recorded as per the SCPE guidelines [165], and functional severity established through classification with the Gross Motor Function Classification System (GMFCS) [166]. The assessment will be videoed and a second blinded assessor will perform this classification for reliability purposes.

#### Bayley Scales of Infant and Toddler Development III (Bayley III)

The Bayley III is a discriminative tool designed to assess cognitive, language and motor development, and social-emotional and adaptive behaviour [167]. It is currently the most widely used assessment tool for overall neurodevelopment in follow up studies of preterm infants between 1 and 3 years CA. It is a norm-referenced test with normative data for the cognitive, language and motor subscales taken from a sample of 1700 American infants and children [167]. Normative data for the adaptive behaviour scale was obtained independently in a sample of 1350 infants and children [167]. Normed scores of the Bayley III have a mean of 100 and a standard deviation of 15, where higher scores reflect better development. The Bayley III motor composite score correlates with the second edition of the Peabody Developmental Motor Skills (r =0.57) [167]. Reliability has been established with the average reliability coefficients for the composite scale scores ranging from .91 (Cognitive) to .93 (Language) [167]. In a systematic review of the predictive value of the Bayley III on development of very preterm infants, mental development index scores were strongly predictive of later cognitive functioning (14 studies with a total sample *n* = 1330 children), r = 0.61 (95 % CI: 0.57–0.64) [168]. Motor scale scores were only moderately predictive of later motor function (across 5 studies with a total sample of *n* = 555 children), r = 0.34 (95 % CI: 0.26–0.42). For this reason, a further two assessments which are primarily motor assessments, and have stronger psychometric properties will be used, the NSMDA and the AIMS [65]. The Bayley III involves interaction between the infant and the examiner in a standardised series of play tasks, and takes 45–60 min to administer at 12 months CA.

#### Neurosensory Motor Developmental Assessment (NSMDA)

The NSMDA is a discriminative and predictive, criterion-referenced test of gross and fine motor development [65, 169]. It examines gross and fine motor performance, neurological status, posture, balance and response to sensory input. The examiner observes and administers items and the test takes 10–30 min to complete. The results give a total score and a functional classification of motor development as normal, or with mild, moderate or severe problems of posture, movement and co-ordination. Assessment at 4 months predicts outcomes at 24 months with a sensitivity of 80 % and a specificity of 56 % [170]. Studies looking at the longer term predictive validity of the NSMDA, found assessment at 12 months had strong associations with motor and cognitive scores at 4 years [171], and NSMDA assessment at 8 months to have an 80 % sensitivity of motor outcomes at 11–13 years in extremely low birth weight infants with no apparent neurological deficit or CP [172]. The NSDMA will be used to classify each infant’s development as normal or as having mild, moderate, severe or profound motor dysfunction at 12 months CA.

#### Alberta Infant Motor Scale (AIMS)

The AIMS is a discriminative, norm-referenced tool that tests gross motor skills through the components of weight bearing, posture and antigravity movements [162, 173]. The test involves observation of the infant in prone, supine, sitting and standing and is able to be completed in this study purely through observation during the Bayley III and NSMDA assessments with no additional handling. Normative data are based on a population of 2200 term infants from 0–18 months in Alberta, Canada [174], and when recently compared with a contemporary sample of 650 Canadian infants, found to still be relevant. Normative data for preterm infants has also been published with a sample of 800 infants born at ≤32 weeks from the Netherlands [175]. Raw scores are obtained with centile ranks and age equivalent growth scores available for term and preterm infants. The AIMS has high inter-rater reliability (ICC = .98 to .99) [176, 177], and intra-rater reliability (ICC = .97-.99) [177]. Concurrent validity with the Bayley II at 12 months CA in a cohort of preterm infants has been established (*r* = .90) [177]. Although the AIMS was not designed as a predictive tool, it has moderate to excellent predictive validity. In a sample of 164 preterm infants assessed at 8 months CA, the AIMS predicted motor outcomes at 18 months CA with a sensitivity 86.4 % and specificity 93 % [178]. The suitability of using the AIMS as a discriminative and predictive tool at 12 months CA in preterm infants has been supported by a clinimetric review of neuromotor measures for preterm infants in the first year of life [65]. The AIMS will be used to classify each infant’s development as normal or suspicious/abnormal at 12 months CA in this study.

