### Sample size

There are no data currently available to assess the relationship between MRI and clinical measures at 30 weeks PMA to predict motor outcome at 3 months CA and motor/neurodevelopmental outcome or CP at 12 months CA. Sample size calculations are based on a study investigating the ability of MRI at TEA, and the GMs assessment, to predict motor outcomes and CP at 12 months CA [6]. In a prospective cohort of infants born <30 weeks GA and in a total sample size of *n* = 86, MRI was classified as normal (*n* = 22), or with mild (*n* = 54), moderate (*n* = 6) or severe (*n* = 4) white matter abnormality (WMA) [93]. Infants with normal or mild WMA were grouped (*n* = 76), and infants with moderate and severe WMA were grouped (*n* = 10) [6]. We assume the same ratio (7.6 MRI normal or with mild/moderate WMA: 1 MRI with moderate/severe WMA) will be observed in this study. Of the *n* = 10 infants in the prior study that had moderate/severe WMA, *n* = 5 (50 %) developed CP [6]. If we assume that 5 % of infants with MRI normal or with mild/moderate WMA develop CP, then the study requires 69 infants to be recruited (8 with MRI with moderate/severe WMA and 61 with MRI normal or with mild/moderate WMA) in order to be able to reject the null hypothesis that the proportion of infants with CP in the two groups are equal with power = 90 %. The Type I error probability associated with this test of this null hypothesis is 0.05. In order to explore WMA earlier, at 30 weeks PMA, and its ability to predict CP at 12 months CA, an increase in the projected numbers will be required, and a further 15–20 % added to account for attrition. Consequently, the aim is to recruit a total sample size of 80 infants with full data sets.

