### Data analysis and statistical considerations

When models involve brain structure and function data from one time point (either 30–32 or 40–42 weeks), standard regression models will be constructed; when models use data from both 30–32 and 40–42 weeks, mixed-effects models that take into account within-infant correlation will be used. Models will be constructed using standard principles; first univariable analyses will be used to identify variables significant at the *p* < 0.15 level and these variables then entered into multivariable models one-by-one, in decreasing order of significance. At each step the current model will be compared to previous models using the likelihood ratio test. Linear regression will be used for continuous outcomes (e.g. diffusion MRI measures of FA and MD); logistic regression for binary outcomes (e.g. disability/no disability); and multinomial logistic regression for categorical outcomes with > 2 categories (e.g. NSMDA categories of normal/suspect/abnormal). Results will be presented as effect estimates and 95 % confidence intervals. The sensitivity and specificity of the predictive assessment model will be determined based on diagnosis of disability using standard definitions. Perinatal, clinical, demographic and social characteristics will be included as covariables when appropriate. Analyses will be supervised by [name], a senior biostatistician at The University of Queensland.

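### The only stated 12-month use of the AIMS is a two-class outcome although a raw score is obtained; regressing the class instead of the score would lose power

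*Protocol article*

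**What the plan says.** The AIMS section of the protocol article describes a graded instrument: "Raw scores are obtained with centile ranks and age equivalent growth scores available for term and preterm infants". It then states one use in this study, to classify each infant's "development as normal or suspicious/abnormal at 12 months CA in this study".

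The section on data analysis and statistical considerations assigns the model by type of outcome. Continuous outcomes go to linear regression, illustrated by FA and MD. Two-class outcomes go to "logistic regression for binary outcomes (e.g. disability/no disability"). The AIMS is named under neither. The same section plans sensitivity and specificity against a diagnosis of disability.

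Primary aims 2 and 3 include prediction of motor outcome at 12 months corrected age. The Bayley III section explains that the NSMDA and the AIMS were added because Bayley motor scores were only moderately predictive of later motor function.

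The only sample-size calculation is for CP by white matter abnormality (WMA) group. It does not involve the AIMS.

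**The concern.** Cutting a score into two classes treats infants just either side of the cut as different and all infants on one side as alike. The measurement costs the same, but the regression has less to work with.

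This matters more in a cohort of about 80, where a low share of abnormal results also means few events. At 10% abnormal there would be 80 × 0.10 = 8 events, against a plan that enters several candidate predictors into multivariable models one at a time. A real association between a 30-week or 40-week measure and 12-month motor performance could be missed because of the form of the outcome. The AIMS was also added to strengthen motor assessment, and its reliability and its correlation with the Bayley II, as cited in the AIMS section, are given as intraclass and correlation coefficients.

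**Working it through.** **1. The plan's own figure.** This checks the protocol's only power statement and shows that it does not concern the AIMS. Inputs from the Sample size section: 8 infants with moderate/severe WMA, 61 others, CP in 50% and 5%, and "The Type I error probability associated with this test of this null hypothesis is 0.05". Two-sided testing is assumed, since the section does not say.

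- Pooled proportion: (8 × 0.50 + 61 × 0.05)/69 = 7.05/69 = 0.102.
- SE under the null: √[0.102 × 0.898 × (1/8 + 1/61)] = 0.114.
- SE under the alternative: √(0.25/8 + 0.0475/61) = 0.179.
- z = (0.45 − 1.96 × 0.1139)/0.1790 = 1.267, so power is 89.7%.

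This reproduces the statement that the study can reject the hypothesis that the two proportions "are equal with power = 90" %. Nothing below changes it.

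**2. Assumptions for the AIMS.** The protocol gives no effect, SD, distribution or abnormal share, so these are assumed: a normally distributed score, a true correlation of r = 0.35 with one continuous predictor, and a share p classed abnormal of 10%, 20% or 30%. Sample sizes: n = 80 is the stated target with full data sets. n = 68 is 80 × 0.85, the number left if 80 are enrolled and 15% are lost.

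**3. Information kept by the class.** With c the normal quantile at p, the efficiency of the class relative to the score is φ(c)²/[p(1 − p)].

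| p | φ(c) | Efficiency | 80 infants count as |
|---|---|---|---|
| 10% | 0.1755 | 0.0308/0.09 = 0.34 | about 27 |
| 20% | 0.2800 | 0.0784/0.16 = 0.49 | about 39 |
| 30% | 0.3477 | 0.1209/0.21 = 0.58 | about 46 |

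**4. Power by formula.** Power = Φ[artanh(r)·√(n − 3) − 1.96]. For the class, r is replaced by r × √efficiency.

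- Score, n = 80: artanh(0.35) = 0.365; 0.3654 × √77 = 3.207; power = Φ(1.247) = 89%.
- Class, n = 80, p = 10%: 0.35 × √0.342 = 0.205; artanh = 0.2077; × √77 = 1.822; power = Φ(−0.138) = 45%. At 20% and 30% it is 59% and 67%.
- Score, n = 68: 0.3654 × √65 = 2.946; power = Φ(0.986) = 84%.
- Class, n = 68: 39%, 52% and 59% at 10%, 20% and 30%.

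**5. Power by simulation.** Test of the correlation on the score against the likelihood ratio test in logistic regression on the class, at r = 0.35:

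| n | Score | Class, 10% | Class, 20% | Class, 30% |
|---|---|---|---|---|
| 80 | about 89% | 46% | 61% | 68% |
| 68 | about 83% | 38% | 55% | 61% |

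Formula and simulation agree to within about 3 percentage points.

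**6. Sensitivity to the assumed effect.** At r = 0.5 and n = 68, power on the class rises to about 71%, 86% and 92%. The efficiencies in step 3 do not depend on r, but the cost in power is smaller when the effect is large.

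**The case against.** The strongest reply is that the text does not confine the AIMS to a class. It says the AIMS will be used to classify infants; it does not say that this is the only use. Raw scores are obtained, linear regression is already planned for continuous outcomes, and the model examples are illustrative and do not name the AIMS. An analysis plan that is not shown may use the score. This stands as a limit: a reader might infer that the AIMS is analysed solely by logistic regression, and the article does not go that far. What remains is that classification is the one use stated, and the score has no stated role in the analysis.

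A class is also legitimate where sensitivity and specificity are wanted, and separating atypical from typical development is a declared purpose. That stands in full, and the class should be kept for it.

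Primary aims 2 and 3 do not rest on the AIMS alone. The Bayley III motor composite is continuous and the NSMDA yields a total score. That stands too, and it limits the consequence.

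A reader might also infer a second error from the norms. The section cites two sets ("Normative data are based on a population of 2200 term infants"; "Normative data for preterm infants has also been published with a sample of 800 infants") and does not say which defines the abnormal class. The share called abnormal could differ between them, but the article gives no gap between the norms from which to size this, and describing both does not show that the choice was left open. A condensed article may leave such scoring detail to a fuller document. It is something to specify, not a separate error.

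**Conclusion.** The point holds as a choice of analysis that can be improved, not as a contradiction. If the AIMS enters the regressions in the only form the article states, power falls from about 89% to 46-68% at 80 infants, and from about 83% to 38-61% at 68. These figures rest on an assumed correlation of 0.35, a normal score and 10-30% classed abnormal; none of these is in the document. The direction does not depend on those values within the range examined, but the size does.

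The consequence for the study is moderate. It should not be read as showing that the study is underpowered or that its sample size is wrong: the 90% power is for CP, reproduces at 89.7%, and is untouched.

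**What to change.** In the AIMS section and the data analysis section, state that the AIMS raw total score, adjusted for exact corrected age at assessment, is the AIMS outcome for regression, using a linear model with residuals checked. The check is needed because the article does not establish linearity or near-normal residuals at 12 months. Keep the normal versus suspicious/abnormal class for sensitivity and specificity. When the wording is revised, also name the norm set and cut that define the class, with the other norm set as a sensitivity analysis.

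The change is to wording only: no new data, visits or handling of infants. The small downside is that a raw-score difference is less directly interpretable than a class, which reporting both largely offsets.
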